### Measurements

Measurements for primary and secondary endpoints will take place at baseline, 3 months (end of the intervention) and 6 months follow-up.

#### Primary study endpoints

##### Physical function

The physical function subscale of the Medical Outcomes Study Short-Form 36 (SF-36) questionnaire will be used as an indicator of patient rated physical functioning.

#### Secondary study endpoints

##### Objective measures of physical function

A battery of tests will be used to assess functional performance [22,23,27]. Tests will be performed in triplicate (except for the 400-m walk which will be performed once) with sufficient recovery time between trials. The best performance on each test will be used in the analyses. The tests will be: 1) timed up and go, 2) 6-meter walk, usual and fast pace, and 3) 400-m walk. Participants with proximal femur bone lesion will be excluded from the 400-m walk test. Performance in each test will be timed electronically using a Kinematic Measurement System (Fitness Technology, SA, Australia).

##### Muscle strength

Dynamic muscular strength of the upper and lower body will be assessed using the one repetition maximum (1RM) method [28]. The 1RM is the maximal weight an individual can move through a full range of motion without change in body position other than that dictated by the specific exercise motion. Participants will perform 1RM tests for the knee extension and chest press exercises using a standard 1RM protocol [23]. Participants with proximal femur bone lesion will be excluded from leg extension 1-RM. Participants with axial skeleton (thoracic/ribs) bone lesion will be excluded from chest press 1-RM. These exercises were selected as they do not involve compression of the spine or excessive load in the pelvic area.

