### Subjects

Ninety men (45 subjects per arm) with prostate cancer and established bone metastases with no regular exercise (undertaking structured aerobic or resistance training two or more times per week) within the past 3 months will be recruited through invitation by their attending specialist in Perth, Western Australia, and the Central Coast region of New South Wales. All participants will require physician consent. Exclusion criteria will include acute illness, significant bone pain, musculoskeletal or cardiovascular or neurological disorders that could inhibit or put them at risk from exercising. The protocol has been approved (ID: 7699 [name]) by the Edith Cowan University Human Research Ethics Committee and all participants will provide written informed consent.

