#### Exercise intervention

The modular multi-modal physical exercise intervention program (M3EP) will comprise resistance, aerobic and flexibility exercises undertaken 3 times per week in an exercise clinic setting supervised by an exercise physiologist. Exercise training sessions will take approximately 60 min (this includes the warm-up and cool-down periods) and will be conducted in the Exercise Clinics at Edith Cowan University in Perth, and at the University of Newcastle's Central Coast campus in Ourimbah. The programme will include 6 exercises that target the major trunk, upper and lower body muscle groups, which we have used in a number of previous studies [21-23,27,43-46] including men on ADT. There will be a modular component for the resistance exercise prescription based on location/extent of bone metastases (Table 2). To ensure the progressive nature of the training program, subjects will be encouraged to work past the specific repetition maximums (RMs) prescribed. The resistance will be increased by 5-10% increment for the next set/training session if subjects are able to perform more repetitions than the RMs specified during a set. Moderate intensity and volume of resistance exercise will range from 10 to 12-RM (e.g. the maximal weight that can be lifted 10 to 12 times) using 3 sets per exercise. This program differs considerably from those commonly prescribed for survivors with localised prostate cancer. Specifically, the M3EP is designed to minimise compressive and shear loads on affected skeletal sites to account for the reduced load bearing capabilities of bone due to metastatic disease in specific regions. Such loading is considerably below the forces exerted on the skeleton during tasks of daily living such as descending stairs or stepping down from a height and will be similar to that of walking. All exercises will be performed at a set cadence of 2 s for both eccentric and concentric phases further minimizing peak forces transmitted to the skeleton. Aerobic exercise component of the M3EP will also be based on location/extent of bone metastases with those with pelvis, axial skeleton (lumbar), proximal femur and all regions bone metastatic disease undergoing non-weight bearing activities (Table 2). The aerobic component will include 20-30 min of cardiovascular exercise using various modes such as walking on a treadmill, cycling or rowing a stationary ergometer, or exercising on a cross training machine based on disease extent (Table 2). Target intensity will be 60%-85% estimated maximum heart rate (220 - age) with individual heart rate monitors (Polar Electro Oy, Finland) provided for each participant. The flexibility component of the M3EP will involve static stretching of all the joint ranges of motion considered important for function. Those with axial skeleton and all regions bone metastases will be excluded from undertaking spine flexion/extension/rotation (Table 2). The protocol will involve 2-4 sets per muscle group at 30-60 s per set as previously proposed [47]. All M3EP sessions will be conducted in small groups of up to 8 participants under direct supervision to ensure correct technique and minimal risk of injury. Each session will commence with a 10-minute warm-up comprising low-level aerobic activities such as treadmill walking and stationary cycling as determined by bone metastases site, as well as stretching and conclude with a 5-minute cool-down period of stretching activities. The M3EP will be designed to provide adequate stimulus to the cardiorespiratory, skeletal and neuromuscular systems while maximizing compliance and retention. All participants will be asked to maintain customary physical activity and dietary patterns over the intervention period (apart from the programmed exercise). Dietary intake will be assessed at baseline, 3 and 6 months using 3-day record. During the course of the study, participants will be required to maintain an activity log and record their recreational physical activities.

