
**Table 2 T2:** Modular multi-modal physical exercise program (M3EP) for prostate cancer with bone metastases

Metastases site	Exercise mode					
	
	*Resistance*			*Aerobic*		*Flexibility*
	**Upper**	**Trunk**	**Lower**	**WB**	**NWB**	**Static **

Pelvis	√	√	√**		√	√

Axial Skeleton (lumbar)	√		√		√	√***

Axial Skeleton (thoracic/ribs)	√*		√	√	√	√***

Proximal Femur	√	√	√**		√	√

All regions	√*		√**		√	√***

√ = Target exercise region; * = exclusion of shoulder flexion/extension/abduction/adduction - inclusion of elbow flexion/extension; ** = exclusion of hip extension/flexion - inclusion of knee extension/flexion; *WB *weight bearing (e.g. walking); *NWB *non-weight bearing (e.g. cycling); *** = exclusion of spine/flexion/extension/rotation.

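### The exclusions from the two maximal strength tests cover only thoracic/rib and proximal femur lesions, so as written a man with a painless shoulder-girdle, humeral or femoral-shaft lesion would still do a maximal lift through that bone

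*Protocol article*

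**What the plan says.** All places are in the protocol article.

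- **Subjects.** The trial enrols men "with prostate cancer and established bone metastases with no regular exercise". No lesion site is required or barred. Physician consent is needed. Significant bone pain is an exclusion, as are "musculoskeletal or cardiovascular or neurological disorders that could inhibit or put them at risk from exercising".
- **Muscle strength.** Participants do 1-RM tests of knee extension (also called leg extension) and chest press, and 1-RM is defined as a maximal load. Two site exclusions follow: "Participants with proximal femur bone lesion will be excluded from leg extension 1-RM" and "Participants with axial skeleton (thoracic/ribs) bone lesion will be excluded from chest press 1-RM". The reason given for the choice of lifts is: "These exercises were selected as they do not involve compression of the spine or excessive load in the pelvic area".
- **Recruitment and Measurements.** Baseline tests come before randomisation. Secondary endpoints are measured again at 3 and 6 months.
- **Exercise intervention and Table 2.** Training is fitted to the lesions: "There will be a modular component for the resistance exercise prescription based on location/extent of bone metastases". The programme is designed to keep load on affected sites low. For proximal femur lesions, among others, Table 2 applies this restriction to lower-body work: "exclusion of hip extension/flexion - inclusion of knee extension/flexion".

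**The concern.** The article lays down a lesion-based rule for who may do a maximal lift, but the sites it names do not match the bones that the lifts load. A chest press passes its load through the humerus and shoulder girdle as well as the chest wall. A leg extension loads the whole femur, not only its upper end. The stated rationale considers the spine and pelvis and does not mention these bones.

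What is at stake is an avoidable fracture risk at a known lesion, in a trial that sets out to show that exercise is safe in these men. Because testing starts before randomisation, the exposure also reaches usual-care men, who receive no training before month 3.

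**Working it through.** **Step 1: the rule applied to men who are eligible on the page.** All are taken to be free of significant bone pain and to have physician consent.

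| Lesion | Chest press 1-RM | Leg extension 1-RM |
|---|---|---|
| Thoracic/ribs | excluded | done |
| Proximal femur | done | excluded |
| Humerus or shoulder girdle only | **done** | done |
| Femoral shaft only | done | **done** |

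The two bold cells are the gap. A man who also has the listed lesion for that test is already protected.

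**Step 2: does another provision close it?**

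- *The training principle.* Low load on affected sites is stated for the exercise programme, not for testing. The article itself is stricter for testing: for a proximal femur lesion, Table 2 keeps knee extension in training, while the Muscle strength section bars the leg extension 1-RM. The training rule therefore cannot stand in for a test exclusion.
- *The bone-pain rule under Safety of the exercise program.* It acts once pain is present, by stopping the exercise programme. It does not prevent a first maximal lift on a painless lesion.
- *Entry conditions.* Physician consent and the at-risk exclusion may stop some of these men. Neither names a lesion site or a fracture-risk criterion.

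**Step 3: what a wider exclusion would cost.** Inputs from Calculation of sample size: SD 12, difference 8, 80% power, two-sided 0.05, dropout about 20%, 90 men randomised.

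The plan's own figure first: n per group = 2 × (1.960 + 0.842)² × (12/8)² = 2 × 7.85 × 2.25 = 35.3, so 36. Then 36/0.8 = 45 per arm and 90 in total. This reproduces. It rests on the SF-36 physical function subscale, so it does not depend on who does the strength tests.

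- Men expected at 3 months: 90 × 0.8 = 72.
- Values per test, before the existing site exclusions and with no loss after month 3: 90 + 72 + 72 = 234.
- Loss per newly excluded man: at most 3 values, 3/234 = 1.3%.
- Rise in the standard error of a test's 3-month group difference when k of n men are lost, about evenly across arms: √(n/(n − k)) − 1.

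| k | n = 72 | n = 36 |
|---|---|---|
| 1 | 0.7% | 1.4% |
| 2 | 1.4% | 2.9% |
| 4 | 2.9% | 6.1% |
| 8 | 6.1% | 13.4% |

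The values of k are illustrative assumptions. So is n = 36, which supposes that the existing exclusions have already halved the test.

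**The case against.** **This is silence in a condensed article.** The lifts follow a cited standard protocol that is not at hand, contraindications for uncommon sites may sit in a fuller document, and the exclusion list in Subjects is not worded as closed. This would succeed if the article said nothing on the matter. It does not: it states which lesions exempt a man from each test and why the lifts were chosen. A stated rule drawn too narrowly can be criticised as it stands. What remains of the objection is that a fuller document might already cover these men.

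**The entry conditions are real cover.** Baseline testing is part of what a man enters, so a specialist who judged a long-bone lesion dangerous should not send him forward. This stands in part. The cover is general and depends on individual judgement, whereas the article thought named sites necessary for the femur and the chest wall.

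**The risk is not shown from the documents.** This also stands in part. That these lifts load these bones is plain biomechanics, but no fracture rate and no frequency of such lesions is given. The Background says that lesions are mainly sclerotic and that spread is commonly to the pelvis and axial skeleton. Among 90 men the number affected could be zero.

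**Stronger readings that a reader might infer, and that the documents do not support:**

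- *That the 400-m walk has the same fault.* Its only site rule is "Participants with proximal femur bone lesion will be excluded from the 400-m walk test". But the Exercise intervention section uses walking as its benchmark for acceptably low loading, so the argument from maximal load does not carry over.
- *That any test loading an affected bone should be barred.* Read literally, this would also remove men with pelvic and lumbar lesions from the walk. Those are the common sites, and the costing above would no longer apply.
- *That training is unprotected because Table 2 has no row for these sites.* The text already prescribes by lesion location and extent, aims for low load on affected sites, and requires direct supervision.

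**Conclusion.** The point holds for the two 1-RM tests and no further. Followed as written, the Muscle strength section sends an eligible man with a painless humeral or shoulder-girdle lesion and no thoracic/rib lesion to a maximal chest press. It sends a man with a femoral-shaft lesion and no proximal femur lesion to a maximal leg extension. Each would face the test at up to three visits, in either arm.

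It is a minor safety fix. The number of men is unknown and probably small, the entry conditions give partial cover, and neither the primary endpoint nor the sample size is affected. The conclusion assumes that no fuller document already adds these sites, and that a maximal lift on a known lesion is a risk worth avoiding. The article's own bar on the leg extension 1-RM for proximal femur lesions supports the second assumption.

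**What to change.** In the Muscle strength section, extend the two existing exclusions:

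- chest press 1-RM: exclude men with a thoracic/rib, shoulder-girdle or humeral lesion;
- leg extension 1-RM: exclude men with any femoral lesion, not only a proximal one.

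The 400-m walk rule and Table 2 can stay as they are, and no general rule on loaded bones is needed.

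The change is an edit to two sentences. The cost is a few missing values on a secondary outcome. An upper-limb lesion costs values on the chest press only, and a femoral-shaft lesion on the leg extension only. As these exclusions follow lesion site and apply from baseline, the same rule governs both arms.

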##### Balance and risk of falling

A Neurocom Smart Balancemaster (Neurocom, OR, USA) will be used to assess static and dynamic balance. This device measures ground reaction force to track whole body centre of pressure and a tilting visual field and support platform to separate the visual, somatosensory and vestibular balance sense of the patient [23]. Falls self-efficacy will be determined using the Activities-Specific Balance Confidence scale [29]. During the course of the intervention, all participants will record any falls that take place and submit monthly fall records to the investigators.

##### Safety of the exercise program

The safety of the exercise program will be assessed by recording the incidence and severity of any adverse events and skeletal complications throughout the intervention. Skeletal complications include pain at known bone metastases sites and pathological skeletal fractures [17]. Bone pain will be monitored according to the Common Terminology Criteria of the National Cancer Institute: grade 1 mild, not interfering with function; grade 2 moderate pain interfering with function but not interfering with the activities of daily life; and grade 3 severe pain, severely interfering with the activities of daily living. In the presence of bone pain, patients will cease the exercise program and undergo standard clinical evaluation, including plain x-rays and other more specialised imaging, as deemed appropriate.

##### Body composition

Regional and whole body lean mass (including appendicular skeletal muscle mass) and fat mass will be derived from a whole body dual-energy X-ray absorptiometry scan (Hologic Discovery A, Waltham, MA). Measurement of trunk adiposity is an important indicator of chronic disease risk, and will be assessed from trunk fat mass obtained from the whole body scan and the ratios of trunk fat to limb fat, and trunk fat to total fat.

##### Muscle density and cross-sectional area

Peripheral Quantitative Computed Tomography (XCT3000, Stratec, Pforzheim, Germany) will be used to measure muscle density (an indicator of fat infiltration within the muscle and hence muscle quality) and muscle cross-sectional areas of the upper and lower limbs [30].

##### Health-related quality of life, bone pain and the late life - function index

Health-related quality of life outcomes on general health, pain, vitality, social functioning, emotional role, and mental health will be measured using the SF-36 [31]. The FACIT-Bone Pain questionnaire will be used to assess the nature, severity and impact of bone pain [32]. The Late Life - Function Index (LL-FI) will be used to assess patient-reported physical functioning [33].

##### Anxiety and depression

The Brief Symptom Inventory-18 will provide a global measure of current psychological distress with subscale scores for anxiety, depression, and somatisation [34].

##### Cancer specific distress

The Impact of Events Scale (IES) and the Memorial Anxiety Scale for Prostate Cancer (MAX-PC) will be used to measure cancer specific distress [35,36]. The IES has 15 items and contains two subscales: Intrusion and Avoidance [36]. Intrusion can also be used as a proxy measure for rumination about cancer. The MAX-PC consists of 18 items and assesses cancer specific distress across three domains: Prostate Cancer Anxiety; Prostate Specific Antigen (PSA) Anxiety; and Fear of Recurrence [35].

##### Fatigue

Fatigue will be assessed using the Functional Assessment of Chronic Illness Therapy-Fatigue (FACIT-F) questionnaire. The FACIT-F is a 13-item scale commonly used to assess fatigue in cancer patients [37] as well as cancer patients receiving exercise interventions [38].

##### Sleep quality

Items from the Pittsburgh Sleep Quality Index (PSQI) will be used to measure sleep quality [39]. The PSQI is used to asses quality of sleep over a 1-month interval, and has been shown to be reliable and sensitive to change [40].

##### Physical activity motivation

The Theory of Planned Behaviour (TPB) is the most widely utilised behavioural framework when examining physical activity motivation in cancer survivors [41]. Therefore, physical activity motivation will be assessed in accordance with the TPB. TPB constructs (affective and instrumental attitude, injunctive and descriptive norm, self-efficacy, perceived behavioural control, intention, and planning) will be assessed in accordance with established guidelines [41].

##### Physical activity level

Self report physical activity level will be assessed by the Godin Leisure-Time Questionnaire. ActiGraph activity monitors (triaxial accelerometer) will be used to objectively assess physical activity levels over a 7-day period [42]. A 6-item sedentary questionnaire will be used to assess the level of sedentary behaviour.

##### Tolerance of the program

Tolerance of the exercise program will be evaluated by recording participants' ratings of perceived exertion on a Borg scale after every exercise session. Additionally, a custom designed survey examining exercise tolerance using a 7-point Likert scale will be administered prior to the first exercise session each week. The number of participants completing the 3-month program as well as the number of sessions attended will be recorded.

#### Other monitoring measures

##### Prostate specific antigen (PSA)

PSA will be assessed at baseline, 3 months (end of the intervention) and 6 months follow-up by an accredited National Association of Testing Authorities laboratory (Pathwest Diagnostics, Perth, Western Australia).

#### Exercise intervention

The modular multi-modal physical exercise intervention program (M3EP) will comprise resistance, aerobic and flexibility exercises undertaken 3 times per week in an exercise clinic setting supervised by an exercise physiologist. Exercise training sessions will take approximately 60 min (this includes the warm-up and cool-down periods) and will be conducted in the Exercise Clinics at Edith Cowan University in Perth, and at the University of Newcastle's Central Coast campus in Ourimbah. The programme will include 6 exercises that target the major trunk, upper and lower body muscle groups, which we have used in a number of previous studies [21-23,27,43-46] including men on ADT. There will be a modular component for the resistance exercise prescription based on location/extent of bone metastases (Table 2). To ensure the progressive nature of the training program, subjects will be encouraged to work past the specific repetition maximums (RMs) prescribed. The resistance will be increased by 5-10% increment for the next set/training session if subjects are able to perform more repetitions than the RMs specified during a set. Moderate intensity and volume of resistance exercise will range from 10 to 12-RM (e.g. the maximal weight that can be lifted 10 to 12 times) using 3 sets per exercise. This program differs considerably from those commonly prescribed for survivors with localised prostate cancer. Specifically, the M3EP is designed to minimise compressive and shear loads on affected skeletal sites to account for the reduced load bearing capabilities of bone due to metastatic disease in specific regions. Such loading is considerably below the forces exerted on the skeleton during tasks of daily living such as descending stairs or stepping down from a height and will be similar to that of walking. All exercises will be performed at a set cadence of 2 s for both eccentric and concentric phases further minimizing peak forces transmitted to the skeleton. Aerobic exercise component of the M3EP will also be based on location/extent of bone metastases with those with pelvis, axial skeleton (lumbar), proximal femur and all regions bone metastatic disease undergoing non-weight bearing activities (Table 2). The aerobic component will include 20-30 min of cardiovascular exercise using various modes such as walking on a treadmill, cycling or rowing a stationary ergometer, or exercising on a cross training machine based on disease extent (Table 2). Target intensity will be 60%-85% estimated maximum heart rate (220 - age) with individual heart rate monitors (Polar Electro Oy, Finland) provided for each participant. The flexibility component of the M3EP will involve static stretching of all the joint ranges of motion considered important for function. Those with axial skeleton and all regions bone metastases will be excluded from undertaking spine flexion/extension/rotation (Table 2). The protocol will involve 2-4 sets per muscle group at 30-60 s per set as previously proposed [47]. All M3EP sessions will be conducted in small groups of up to 8 participants under direct supervision to ensure correct technique and minimal risk of injury. Each session will commence with a 10-minute warm-up comprising low-level aerobic activities such as treadmill walking and stationary cycling as determined by bone metastases site, as well as stretching and conclude with a 5-minute cool-down period of stretching activities. The M3EP will be designed to provide adequate stimulus to the cardiorespiratory, skeletal and neuromuscular systems while maximizing compliance and retention. All participants will be asked to maintain customary physical activity and dietary patterns over the intervention period (apart from the programmed exercise). Dietary intake will be assessed at baseline, 3 and 6 months using 3-day record. During the course of the study, participants will be required to maintain an activity log and record their recreational physical activities.

**Table 2 T2:** Modular multi-modal physical exercise program (M3EP) for prostate cancer with bone metastases

Metastases site	Exercise mode					
	
	*Resistance*			*Aerobic*		*Flexibility*
	**Upper**	**Trunk**	**Lower**	**WB**	**NWB**	**Static **

Pelvis	√	√	√**		√	√

Axial Skeleton (lumbar)	√		√		√	√***

Axial Skeleton (thoracic/ribs)	√*		√	√	√	√***

Proximal Femur	√	√	√**		√	√

All regions	√*		√**		√	√***

√ = Target exercise region; * = exclusion of shoulder flexion/extension/abduction/adduction - inclusion of elbow flexion/extension; ** = exclusion of hip extension/flexion - inclusion of knee extension/flexion; *WB *weight bearing (e.g. walking); *NWB *non-weight bearing (e.g. cycling); *** = exclusion of spine/flexion/extension/rotation.

